Based on the approach used in the successful Eclampsia and Magpie Trials, we will develop '**pre-eclampsia boxes**' for use by chHCPs. These boxes will include single doses of oral methyldopa (750mg) and i.m. MgSO4 (10g in two 5g vials of 50% solution), along with all necessary supplies and disposal measures. Women will not receive further MgSO4 until they reach a CEmOC facility. There, they will receive a further dose according to local protocols. As part of facility enhancement, personnel at CEmOC facilities will be educated about how to deal with those women enrolled in CLIP who are transported to facilities. Through these enhancement activities, described below, we will encourage standardised dosing regimens in line with international guidelines such as 2g i.v. MgSO4 over 10-15 minutes for recurrent eclampsia (that occurred en route or at facility). Through CPD activities, we will suggest optimal treatment protocols for CLIP women referred to facilities. **Following administration of 10g i.m. of MgSO4 in the community:**

- Women will not receive further MgSO4 therapy until they have reached a CEmOC facility
- At the CEmOC facility, these women will receive more MgSO4 ONLY after at least 4 hr have passed since their initial 10g i.m. MgSO4 loading dose given in the community.

- If women arrive at the CEmOC facility 4-6hr after receiving a 10g i.m MgSO4 loading dose in the community, these women should receive MgSO4 maintenance therapy, consisting of either: (i) 5g i.m. every 4hr, or (ii) 1g/hr i.v.
- If women arrive at the CEmOC facility >6hr after receiving a 10g i.m MgSO4 loading dose in the community, these women should receive another loading dose of MgSO4 following by maintenance therapy, as follows: (i) 10g i.m. plus 4 g i.v. loading dose, followed by 5g i.m. every 4 hr as maintenance therapy, or (ii) 4g i.v. loading dose, followed by 1g/hr i.v. maintenance therapy.

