## 2.3 RISKS TO THE SAFETY OF PARTICIPANTS

The main risk of the CLIP intervention is that it may lull cHCPs, families, and the women themselves into a false sense of security, thereby delaying the initiation of transport for definitive and life-saving treatment. It is for this reason that the CLIP package of care will include education about appropriate transport to facility,

as well as instructions about how quickly that transport should occur.

For methyldopa safety, we will identify the percentage of women with an 'out of target' BP on admission to facility (i.e., sBP  $\geq 160$  mmHg indicating lack of effect, or sBP  $< 110$  mmHg indicating excessive effect).

MgSO4 toxicity is not a major concern. Mg2+ is renally cleared but even if a woman were anuric, one 10g i.m. loading dose of MgSO4 would not result in serum Mg2+ concentrations sufficient to cause neuromuscular blockade. However, given that repeat doses would have the capacity to do so, no repeat doses of i.m. MgSO4 will be given in the community by cHCPs (or at a PHC with only BEmOC capabilities), even if the indication for therapy persists. Practically, we will assess MgSO4 injection site haematomas, infections and pain using standardised assessment tools in women who received the particular intervention. cHCPs will be trained in proper methods of administration of i.m. injections and all women who receive an injection will be referred to a local facility for follow-up in order to minimize any risks related to these side effects.

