| Treatment                                                                                                             | 
 
◇ 200mg labetalol p.o. or 10mg nifedipine p.o. or hydralazine 5mg IV for severe hypertension (sBP <math>\geq 160</math>mmHg); maintenance therapy titrated against response; parenteral antihypertensives as required
 
◇ MgSO4 loading dose (IV/IM if not already administered in the community or 10g IM MgSO4 was administered more than 4 hr prior to facility admission) for women with severe hypertension or vaginal bleeding (as indicators of severe pre-eclampsia) or eclampsia (single); MgSO4 dose of 2g IV for women who had a seizure after the 10g IM MgSO4 was administered in the community. Then, maintenance therapy (usually 1g/h) until 24 hours postpartum.
 
◇ Arrangements made for definitive therapy 
 
◇ If >local threshold for viability (e.g., 28 weeks' by best clinical estimate), <34+0 weeks', and PIERS probability <25%: administer 12mg dexamethasone i.m. x 2 12h apart, wait 48h and deliver (transfer to regional centre, if relevant)
 
◇ If <viability, <math>\geq 34+0</math> weeks', or PIERS probability <math>\geq 25\%</math>: deliver
 
 
 
 |

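### Section 2d and Table 4 give incompatible facility MgSO4 instructions for women with a Table 4 indication who arrive 4-6 hours after the community dose

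*Protocol*

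**What the plan says.** Section 2d (intramuscular MgSO4) ends with bullets on what follows the community dose. The first facility rule is that women get more MgSO4 "ONLY after at least 4 hr have passed since their initial 10g i.m". dose. The next bullet begins "If women arrive at the CEmOC facility 4-6hr after receiving a 10g i.m". dose and prescribes "maintenance therapy, consisting of either: (i) 5g i.m. every 4hr, or (ii) 1g/hr i.v". The last begins "If women arrive at the CEmOC facility >6hr after receiving a 10g i.m". dose and prescribes a further loading dose followed by maintenance.

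Earlier in the same section, facilities are to be encouraged to use standard regimens, with the example of 2 g i.v. MgSO4 "over 10-15 minutes for recurrent eclampsia (that occurred en route or at facility").

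The hospital treatment row of Table 4 covers the same situation. It lists a loading dose if none was given in the community, or if the 10 g i.m. dose "was administered more than 4 hr prior to facility admission". The indications named are severe hypertension, vaginal bleeding and eclampsia. The row then gives a "dose of 2g IV for women who had a seizure after the 10g IM" community dose, followed by maintenance until 24 hours postpartum.

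**The concern.** Facility staff could follow either text in good faith and treat the same woman differently. For a woman arriving between the two thresholds, one text withholds a second loading dose and the other lists it.

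Two things are at stake. The first is patient safety: Section 2.3 treats a single 10 g dose as safe and restricts repetition in the community "given that repeat doses would have the capacity to do so", so the timing of later MgSO4 is a matter the protocol itself takes seriously. The second is standardisation. Section 2.5 relies on a consistent level of facility care across clusters to limit bias and contamination. Component 3 undertakes to train facility staff in the CLIP protocol and in managing these women once they arrive. A protocol holding two incompatible versions cannot support one standard.

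**Working it through.** No sample size, power, alpha or event figure is involved, so there is nothing to recompute. The check sets the two texts side by side by time from community dose to arrival.

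| Time since community dose | Section 2d | Table 4, hospital treatment | Compatible? |
|---|---|---|---|
| Under 4 h, no new seizure | No more MgSO4 until 4 h have passed | No loading dose; maintenance listed without a time condition | Agree on no reloading; start of maintenance unclear |
| Under 4 h, new seizure | Bullet: nothing before 4 h. Earlier sentence: 2 g i.v., no interval stated | 2 g i.v., no interval stated | 2d is at odds with itself; its earlier sentence agrees with Table 4 |
| More than 4 h, up to 6 h | Maintenance; reloading kept for later arrivals | Loading dose, then maintenance, for the listed indications | No |
| Over 6 h | Loading dose, then maintenance | Loading dose, then maintenance, for the listed indications | Yes |

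**Width of the main conflict.** At exactly 4 hours Table 4's condition is not yet met. At exactly 6 hours the 2d maintenance bullet still applies. The conflict therefore runs from just over 4 hours to 6 hours: 6 − 4 = 2 hours.

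**Can both be satisfied?** Take a woman with severe hypertension who arrives at 5 hours. Section 2d gives her maintenance; Table 4 gives her a loading dose and then maintenance. The 2d bullets apply to all women given the community dose, so Table 4 cannot be read as covering a group that 2d leaves out. Table 4 has no 4-6 hour band that might be a shortened form of the 2d rule. No reading meets both.

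**Who is affected.** Table 4's community rows also allow MgSO4 for stroke and for a miniPIERS probability of at least 25%. The hospital loading line does not name these two. The conflict is therefore shown only for women with severe hypertension, vaginal bleeding or eclampsia.

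**Can the window be reached?** The Section 2b triggers that lead to MgSO4 also call for urgent transport, defined as within 4 hours, so the main conflict concerns women who miss that target. The protocol does not assume the target is always met: Section 2.13 measures it as compliance, and Section 2b leaves families in Nigeria and Pakistan generally responsible for finding and paying for transport. The seizure ambiguity concerns the earlier period, including women transported on time.

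**The case against.** The strongest reply is that facility care is not the trial's treatment. Table 4 heads the hospital block as unfunded by the trial, though an expected standard of care. Section 2d refers to local protocols and speaks of encouraging and suggesting regimens. Section 2.7 says women receive the standard in place at the facility. This lowers the severity, but it does not remove the error: the trial gives the community dose and undertakes to teach facilities what to do next, so its own advice should be single and consistent.

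On seizures, a reader might infer that the text and the table oppose each other. They do not. The recurrent-eclampsia sentence in 2d agrees with Table 4, and both sit uneasily with the 4-hour bullet. The sentence could be meant as an exception to that bullet, but the bullet states none.

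Four stronger inferences are tempting, and the documents do not support them:

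- **That the MgSO4 safety comparison is distorted.** Section 2.15 defines the systemic events (respiratory depression, coma or death during transport) as diagnosed on arrival, before any facility dose. Only injection-site haematoma or infection counts events after facility administration.
- **That only one arm is exposed.** The CLIP package is withheld from control clusters, but Appendix A describes Indian ANMs as expected to give 10 g i.m. for eclampsia before referral, and control clusters keep current practice.
- **That every woman arriving at 4-6 hours is affected.** Table 4's loading line covers only the listed indications, and women given no community MgSO4 fall outside the conflict.
- **That Section 2.3 argues against facility reloading.** The rule it draws concerns the community and PHCs with only basic emergency obstetric capability.

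**Conclusion.** The contradiction holds in a limited form. For women with severe hypertension, vaginal bleeding or eclampsia who arrive more than 4 and up to 6 hours after the community dose, Section 2d and Table 4 cannot both be followed. Over 6 hours they agree. Under 4 hours, two points need clarifying: whether the 4-hour bullet allows an exception for a new seizure, and whether Table 4's maintenance is subject to a minimum interval.

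The number of women cannot be given, because the documents report no distribution of arrival times. If all treated women arrived within 4 hours, no one would meet the main conflict; otherwise it reaches the late arrivals in the 2-hour window who have a listed indication. No estimate, power figure or primary analysis depends on the point. It needs correcting because it gives incompatible drug instructions for severely ill women and weakens the claim of standardised facility care. The conclusion rests on the wording alone and takes no position on which instruction is clinically right.

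**What to change.** The clinical leads, with DSMB review, should reconcile the Section 2d bullets and the hospital row of Table 4 into one instruction. It should state separately what applies under 4 hours without a new seizure, under 4 hours with one, at 4-6 hours and after 6 hours, with the boundary times assigned unambiguously. It should also say to which indications it applies and whether maintenance is subject to a minimum interval. That single text should then be used in all facility-enhancement activity, and any facility already taught from either version should receive it. No regimen is proposed here.

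The cost is a protocol edit in two places, DSMB review and consistent teaching material. Outcomes, sample size and analysis are unchanged.

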**FIGURE 11. Ogun State, Nigeria**

Putting the physical location of the CLIP Trial into context

[figure not shown]

**Figure 12** Maputo Province, Mozambique  
Putting the physical location of the CLIP Trial into context

[figure not shown]

**Figure 13. Hyderabad and Matiari Districts, Sindh Province, Pakistan**

Putting the physical location of the CLIP Trial into context

[figure not shown]

**Figure 14. Belgaum and Bagalkot Districts, Karnataka State, India**

Putting the physical location of the CLIP Trial into context

## Appendix A – Summary of site visit and initial Feasibility Study findings

### ***Partnerships***

The following stakeholders have been engaged and have provided support for the trial:

#### ***World Health Organization Department of Maternal, Newborn, Child and Adolescent Health (MNCAH)***

The chair of the PRE-EMPT objective 5 (knowledge translation) group is [name], from this WHO department. The MNCAH group was instrumental in co-ordinating the development of the 2011 WHO pre-eclampsia guidelines, and will be instrumental in updating the guideline to reflect the findings of

the CLIP trial, and in promulgating the results of the CLIP trial to key decision makers in LMICs. [name] is a member of the advisory group advising on maternal mortality and morbidity methods for CLIP.

***UNDP/UNFPA/WHO/World Bank Special Programme of Research, Development and Research Training in Human Reproduction (RHR)***

The WHO RHR group have been important partners in the PIERS research agenda ([name] and [name]), as well as for objectives 1 ([name]) and 5 ([name]) of the PRE-EMPT project.

***Royal College of Obstetricians and Gynaecologists (RCOG)***

We have developed a partnership with the RCOG (London) International Office (Senior Vice-President [name]). An element of the RCOG's international mandate is to strengthen the capacity of inpatient facilities in LMICs in terms of the use of evidence-based care. We will co-ordinate our activities in Nigeria, Mozambique, Pakistan, and India so that the RCOG will support public and private facility capacity building in the referral centres in Nigeria (Sagamu), Mozambique (Manihça and Maputo), Pakistan (Matiari, Hyderabad and Karachi), and India (Belgaum and Bagalkot). This commitment of time, energy and expertise will ensure that women in the study clusters will receive timely and effective care in the centres to which they are referred.

***Society of Obstetricians and Gynaecologists of Canada (SOGC)***

We have developed a partnership with the SOGC International ALARM Course team. An element of the SOGC's international mandate is to strengthen the capacity of inpatient facilities in LMICs in terms of the use of evidence-based care. We will co-ordinate our activities in Nigeria, Mozambique, Pakistan, and India so that the SOGC will support public and private facility capacity building in the referral centres in Nigeria (Sagamu), Mozambique (Manihça and Maputo), Pakistan (Matiari, Hyderabad and Karachi), and India (Belgaum and Bagalkot). This commitment of time, energy and expertise will ensure that women in the study clusters will receive timely and effective care in the centres to which they are referred.

***USAID/MCHIP (Maternal & Child Health Integrated Program)***

We have developed a partnership with MCHIP, particularly through [name] (PRE-EMPT TAG member). MCHIP is the USAID Bureau for Global Health's flagship programme focussed on maternal, neonatal and child mortality reduction and acceleration of progress towards MDGs 4 and 5. An element of MCHIP's mandate is to strengthen the capacity of inpatient facilities in LMICs in terms of the use of evidence-based care. We will co-ordinate our activities in Nigeria, Mozambique, Pakistan, and India so that the MCHIP will support public and private facility capacity building in the referral centres in Nigeria (Sagamu), Mozambique (Manihça and Maputo), Pakistan (Matiari, Hyderabad and Karachi), and India (Belgaum and Bagalkot). This commitment of time, energy and expertise will ensure that women in the study clusters will receive timely and effective care in the centres to which they are referred.

***Current practice - the provision of maternity care and pre-eclampsia interventions***

***Nigeria***

Antenatal care is delivered at the primary health centre level. Most women attend antenatal care every 3-4 weeks up to 28 weeks gestation, every 2 weeks till 36 weeks gestation and weekly thereafter. A typical antenatal visit does include blood pressure measurement and proteinuria testing by indication. Few clinics have a laboratory or ultrasound capacity. Much of obstetric services are paid out of pocket. Few PHCs have ambulance services for referral of complex cases.

Care is accessed through both public and private facilities throughout OGUN State with an estimated 40% of women accessing care through private institutions and 60% attending public facilities.

### ***Community Health Extension Worker (CHEW) training & current scope of practice***

Community Health Extension Workers (CHEW) are responsible for delivery of primary health care services in Nigeria. They work both in the community and clinic settings; however due to workload restraints CHEWs often remain stationed predominantly at the PHC. The training and regulation of practice is under the jurisdiction of Community Health Practitioners' Registration Board of Nigeria. The CHEW program includes certification in community health, practical exercises and examinations, supervised clinical experience and supervised community experience. The areas of focus for CHEW training relevant to CLIP are: English training, computer education, medical sociology, reproductive health, clinical skills, and referral system and outreach services. The current CHEW curriculum does not include specific training for management or diagnosis of pre-eclampsia/eclampsia or any other pregnancy complication.

### ***Health Assistants (HA's) training & current scope of practice***

The HA's are admitted into the health assistant training program with a secondary school certificate (high school qualification) either at registered private or government training institutions. They work almost entirely in private institutions after completion of their training. They undergo training for three years at these training institutions and assist the trained nurse midwife with care of patients and pregnant women in the community. They are trained to take vital signs, collect preliminary clinical history of symptoms and signs from patient and take pregnant history from patronizing pregnant women at private clinics, where they exist. At the private institutions, Health Attendants are trained to give intramuscular drugs/injections, take normal deliveries and they do give injections when prescribed by doctors in the private clinics.

### ***Mozambique***

The Mozambique health system is largely supported by foreign aid . There are significant human resource shortages which require task shifting for obstetric care services. Countrywide, there is a low number of available skilled birth attendants. Access to primary health care facilities, where antenatal care is delivered, is also low . The first antenatal visit is typically delayed until the 2nd or 3rd trimester, with 84% coverage for at least one antenatal visit during pregnancy . As a result of these constraints the majority of births are rural many without skilled attendants.

Magnesium sulphate has long been used in Mozambique for the management of pre-eclampsia and eclampsia, however, its use has been primarily at central hospitals and alternative anti-seizure medications have been used in the periphery .

### ***Agente Comunitarios de Saude (ACS) training & current scope of practice***

Agente Comunitarios de Saude (or basic multi-task health care helpers) help to promote health in their communities; constituting the link between them and the national health system. ACSs are recruited from within the community and receive six months' training to provide basic preventive (community health education) and curative community based-care for diarrhoea, pneumonia and malaria, focussing on the widespread use of diagnostics and appropriate treatment. The ACSs allow isolated populations to have access to basic health care and essential drugs for high burden diseases like malaria, and act as an entry point for referral to higher level health services, providing basic first aid before transfer where needed.

### ***India***

The Government of India has recently committed to the National Rural Health Mission. This initiative aims to obtain universal skilled birth attendance across the country. The National Rural Health Mission highlights the role of ANMs in providing antenatal care, timely referrals, and provision of treatment in emergency obstetric cases. Health care workers providing obstetric care at the community level are ANMs,

ASHAs and Anganwadi Workers. Each antenatal visit should include: a medical history, physical exam, abdominal exam, laboratory investigations, clinical interventions (IFA supplement, TT injection, malaria), and health promotion counselling. A minimum of four antenatal visits for all pregnancies is encouraged: before 12 weeks, 12-26 weeks, 28-34 weeks and 36 weeks-term.

Facilities are generally equipped to manage cases of pre-eclampsia and eclampsia. Due to concerns regarding safety and availability diazepam is frequently used in place of  $\text{MgSO}_4$ .

### ***Auxiliary Nurse Midwife (ANM) training & current scope of practice***

Training for Assistant Nurse Midwives includes a wide range of health competencies: understanding of holistic health/social determinants of health, ability to mobilize communities, provide emergency care, treatment of minor ailments, midwifery services and referral, basic neonatal care and referral, child services, guide and train TBAs and AWWs, health counselling, participate in National programmes, collaborate with community organizations, manage health care settings. Their midwifery services include care during pregnancy, intrapartum and postpartum.

They are expected to measure blood pressure at every visit and test for albumin in the cases of high blood pressure. If a woman is identified with high blood pressure the ANM is responsible to referral to a 24 hour PHC to initiate antihypertensive therapy. ANMs also follow-up and advise of the warning symptoms. In cases of eclampsia the ANM should ensure safety, give  $\text{MgSO}_4$  (10g i.m.) and refer to a facility within two hours.

### ***Accredited Social Health Activist (ASHA) training & current scope of practice***

ASHAs are local women trained to act as health educators and promoters in their communities. They receive a total period of 28 days' training in five episodes. However, this core training is supplemented by ongoing CPD activity in parallel with the development of necessary skills and expertise through on the job training. After a period of 6 months of functioning in her village, she is then sensitised to issues related to HIV, AIDS, and STIs (prevention and referral), as well as trained on newborn care.

Their tasks include motivating women to have a facility birth, bringing children to immunisation clinics, encouraging family planning, treating basic illness and injury with first aid, keeping demographic records, and improving village sanitation. In addition, ASHAs are central to communication between the health care system and rural populations.

